### Study timeline

The participant timeline is presented in table 1.

**Table 1 T1:** Schedule of enrolment and measurements

Timepoint	Enrolment	Screening	Visit 1	Visit 2	Visit 3
	- 2 weeks	Baseline		3 months	6 months
Eligibility screen	x				
Informed consent		x			
Transient elastography		x		x	x
Length		x			
Weight		x		x	x
Waist circumference			x	x	x
Body composition			x	x	x
Grip strength			x	x	x
Blood pressure			x	x	x
Laboratory measurements			x	x	x
Physical activity			x		x
SF-36 questionnaire			x	x	x
3-day food diary			x	x	x
Questionnaire demographics, lifestyle and medication			x	x	x
Consultation with dietitian (eTRE-MD group)			x	x	x
Medication dispensing (N/B group)			x	x	x

eTRE-MD, early time restricted eating Mediterranean diet; N/B, naltrexone/bupropion; SF-36, 36-Item Short Form Health Survey.

### Sample size and recruitment

Little is known in the literature about the effect of N/B on liver fibrosis. A recent study showed a decrease in LSM from 4.67 kPa to 4.14 kPa after 6 months of N/B use.^31^ The relevance of this finding is unclear, since LSM values <7.0 kPa are considered to be not clinically relevant. Studies in which participants followed a Mediterranean diet for 6 months show varying outcomes. Two studies showed that it has an average decrease of 0.4 to 2.1 kPa in liver fibrosis.^32 33^ To calculate the effect size, we took a mean difference of the two dietary studies (1.3 kPa), the mean of the N/B group (0.5 kPa) and an SD of 1.0 kPa, which is based on expert opinion due to lack of evidence in the literature. This leads to an effect size of 0.8 kPa. In this study, we will perform a two-sided hypothesis test to assess whether there is a difference in LSM after 6 months between the eTRE-MD group and N/B group. The null hypothesis (H0) states that there is no difference in LSM between the groups, while the alternative hypothesis (H1) assumes a difference of 0.8 kPa or more. Based on an effect size of 0.8 kPa with an SD of 1.0 kPa, a significance level of 0.05 and power set to 0.80, we calculated that 29 participants per group are needed. Assuming a drop-out of 10%, inclusion will be 70 participants (35 participants per group). Unpublished data from ongoing research within our department show that about 20% of people with one or more cardiometabolic risk factors in the Netherlands have a transient elastography result >7.0 kPa. This means that to include 70 patients, we will need to screen about 350 people. It is likely that the planned number of participants can be recruited as 3000 people with cardiometabolic risk factors are seen at the outpatient clinic every year. The patient population not treated at the hospital will be referred by the general practitioner when MASLD is suspected.

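### The printed sample-size inputs give 26 per group, not 29, and a 10% drop-out allowance on 29 gives 66 participants, not 70; both gaps are conservative at the stated 0.8 kPa, and the text needs correcting

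*Protocol article*

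**What the plan says.** All the figures stand in the protocol article under Sample size and recruitment.

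- **Planning difference.** For the diet arm: "Two studies showed that it has an average decrease of 0.4 to 2.1 kPa in liver fibrosis". The authors then write that "we took a mean difference of the two dietary studies (1.3 kPa), the mean of the N/B group (0.5 kPa", and arrive at 0.8 kPa. The alternative hypothesis is set at that value or more.
- **Spread.** They use "an SD of 1.0 kPa, which is based on expert opinion due to lack of evidence in the literature".
- **Test.** "we will perform a two-sided hypothesis test", with "a significance level of 0.05 and power set to 0.80". The section does not name the test or formula.
- **Result.** The inputs are drawn together as "Based on an effect size of 0.8 kPa with an SD of 1.0 kPa, a significance level of 0.05 and power set to 0.80", and the sentence goes on: "we calculated that 29 participants per group are needed. Assuming a drop-out of 10%, inclusion will be 70 participants (35 participants per group".
- **Screening.** About 20% of people with a cardiometabolic risk factor are said to exceed 7.0 kPa, and from this: "This means that to include 70 patients, we will need to screen about 350 people".

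**The concern.** Two successive results in one paragraph cannot be reproduced from the inputs printed beside them. The first is the number per group and the second is the inflation for drop-out. This paragraph is the only support for the statement, under Strengths and limitations, that the planned size gives adequate power. The SD is already a matter of expert opinion, so the other inputs should at least be traceable. As printed, a reader cannot tell whether the calculation used 0.8 kPa or a smaller unrounded value, whether drop-out entered once or twice, or how much loss the trial can absorb before falling below 80% power.

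**Working it through.** **Inputs (Sample size and recruitment; 1:1 allocation from Randomisation).** Difference 0.8 kPa, SD 1.0 kPa, two-sided alpha 0.05, power 0.80, drop-out 10%, 20% of those screened above 7.0 kPa.

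**Step 1: number per group at 0.8 kPa.** The normal approximation is n = 2 × (1.96 + 0.8416)² × SD² / difference².

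- Normal approximation: 2 × 7.849 × 1 / 0.64 = 24.5, so 25 per group.
- Two-sample t-test (noncentral t): 25.5, so 26 per group.
- One-sided t-test, for comparison: 20.03, so 21.
- Wilcoxon test, dividing 25.5 by an efficiency of 0.955 or by the minimum of 0.864: 27 or 30.

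None of these gives the stated 29.

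**Step 2: what does give 29.** Two routes match.

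- *Unrounded difference.* The midpoint of 0.4 and 2.1 is 1.25, and 1.25 − 0.5 = 0.75 kPa. The t-test then needs 28.9, so 29 (28 by normal approximation).
- *Drop-out already included.* 26 / (1 − 0.10) = 28.9, so 29.

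The two routes mean different things. In the first, 29 is the evaluable number for 0.75 kPa. In the second, 29 is the enrolled number for 0.8 kPa, and going on to 35 adds a second allowance.

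**Step 3: inflation for drop-out.**

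- Per group: 29 / 0.9 = 32.2, so 33, and 66 in total.
- On the total: 58 / 0.9 = 64.4, so 65.
- Adding 10% instead of dividing by 0.9: 29 × 1.1 = 31.9, so 32, and 64 in total.

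No convention gives 70. The loss that 35 per group can absorb while leaving 29 is 1 − 29/35 = 17.1%.

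**Step 4: power (two-sample t-test, SD 1.0, two-sided 0.05).** With 35 enrolled and 10% lost, 35 × 0.9 = 31.5, taken as 31.

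| Evaluable per group | 0.80 kPa | 0.75 kPa |
|---|---|---|
| 26 | 80.8% | 75.6% |
| 29 | 84.9% | 80.1% |
| 31 | 87.3% | 82.8% |
| 35 | 91.0% | 87.1% |

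**Step 5: screening.** 70 / 0.20 = 350, which reproduces the stated figure. Eligibility criteria, however, also cap stiffness below 13.6 kPa, and the 20% is not restricted by that cap. If a share f of those above 7.0 kPa is finally enrolled, the number is 70 / (0.20 × f). The documents give no value for f. As an illustration only, f = 0.9 gives 389, 0.8 gives 438, 0.7 gives 500 and 0.5 gives 700.

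**The case against.** The strongest defence is that nothing here harms the trial. The stated target is 0.8 kPa, used as effect size, as alternative hypothesis and as calculation input. At that value both deviations err towards a larger trial. Rounding 1.25 to 1.3 is ordinary rounding, and 66 may simply have been rounded up to 70. All of that stands. It lowers the severity but does not make the printed figures follow from the printed inputs, and the text mentions no rounding up.

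Several stronger readings are tempting and are not supported.

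- *That 29 was certainly computed from 0.75 kPa.* This is plausible, but 26/0.9 fits as well, and the document does not settle it.
- *That the trial is underpowered because the unrounded inputs give 0.72 kPa.* The cited naltrexone/bupropion fall, 4.67 to 4.14, is 0.53 kPa, and 1.25 − 0.53 = 0.72 kPa would need 31.3, so 32 per group. But the protocol says it used 0.5 kPa. Even at 0.72 kPa, 31 evaluable per group gives about 80%.
- *That 350 is miscalculated or ignores all other eligibility limits.* The division is right, and the 20% already refers to people with a risk factor. Data collection also places a telephone discussion of the criteria, a reflection period and the patient's agreement before elastography. What remains is narrower. A telephone call cannot detect a value at or above 13.6 kPa, and consent is signed only after the scan. No allowance is shown for these or other residual losses.
- *That recruitment is infeasible.* With 3000 people with risk factors seen at the clinic each year, the screening arithmetic alone does not show this.

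**Conclusion.** Two mismatches are confirmed. The printed inputs require 26 per group by t-test rather than 29. Applying 10% drop-out to 29 gives 66 participants rather than 70, while 35 per group covers about 17% loss. The origin of 29 is undetermined between the two routes above.

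At the stated 0.8 kPa the trial is larger than its inputs require, with 84.9% power at 29 per group and about 87% at 31. At 0.75 kPa it still reaches 80.1% and about 83%. These figures assume a two-sample comparison of change with the printed SD of 1.0 kPa; they do not test whether that SD is right. The arithmetic therefore does not undermine the planned 70. This is a low-severity reporting error. The screening figure is correct as a division and is best read as a minimum.

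**What to change.** Keep 70 participants and correct the text of Sample size and recruitment.

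1. State the unrounded planning difference and the test actually used, with the number and power that follow. If the difference is 0.8 kPa, this is 26 per group for 80% power, or 87% with 31 evaluable per group. If it is 0.75 kPa, this is 29 per group for 80%, or 83% with 31. The sponsor should choose from its own calculation record, since the document does not show which applies.
2. State that 35 per group covers about 17% loss, or that 66 was rounded up to 70. If 29 already contains the 10% allowance, say so.
3. Label the screening figure of about 350 a minimum. Note that the 20% yield does not apply the upper stiffness limit and that nothing is added for residual ineligibility or refusal.

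The cost is a few sentences. Enrolment, design and analysis are unchanged.

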### Randomisation

After signing informed consent, participants will be randomised to either the eTRE-MD group or N/B group. A 1:1 randomisation will be performed via a data management system (Castor Electronic Data Capture (EDC), Amsterdam, The Netherlands) in blocks of 2, 4 and 6. Results from the randomisation will be communicated to the participant after the baseline measurements. The resulting randomisation list will be managed by the secretary of the department of Internal Medicine in the Franciscus hospital. Participant blinding will not be done, as blinding is impossible considering this type of intervention. However, the first preliminary statistical analyses of the primary outcome will be performed by an independent statistician, blinded for the allocation.

### Data collection

The recruitment, enrolment and data collection are conducted by the investigator, who is also responsible for delivering the interventions. Before the start of the study, the investigator will hold a pre-screening by phone to explain the study and discuss the inclusion and exclusion criteria. The patient is given at least 2 weeks for reflection. If the patient agrees to participate, a screening will be scheduled at the Franciscus hospital to determine the degree of liver fibrosis using transient elastography (Fibroscan).

If the participant meets the inclusion criteria, they will sign a consent form together with the researcher during the same visit, and the baseline measurements and randomisation will be performed. After 3 months (visit 2) and 6 months (visit 3), the same measurements are performed as at baseline (visit 1) (table 1). Participants in both groups will have an appointment by phone with the researcher after 2 weeks to check whether the diet or medication is being used properly and whether complaints have occurred.

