**Trial registration number:**

NCT06845345.

Strengths and limitations of this studyThis study uses a randomised controlled design to compare two active interventions.The planned sample size provides adequate statistical power to detect between-group differences.Blinding is not feasible because the interventions differ substantially, but the primary outcome is an objective clinical measure with low risk of bias.Liver steatosis and fibrosis are assessed using transient elastography rather than liver biopsy, which is the diagnostic gold standard.

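### The investigator who delivers the interventions also collects the follow-up stiffness data, and only a preliminary analysis is blinded, so the claim of low risk of bias is not supported

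*Protocol article*

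**What the plan says.** Four places in the protocol article bear on this.

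- **Data collection**: "The recruitment, enrolment and data collection are conducted by the investigator, who is also responsible for delivering the interventions". The same section says that the baseline measurements are repeated at 3 and 6 months. Table 1 lists transient elastography, the primary outcome, at both visits.
- **Randomisation**, on participants: "Participant blinding will not be done, as blinding is impossible considering this type of intervention". No blinding of the outcome assessor is described.
- **Randomisation**, on analysis, offered as a counterweight to the open design: "the first preliminary statistical analyses of the primary outcome will be performed by an independent statistician, blinded for the allocation".
- **Strengths and limitations box** after the abstract: "Blinding is not feasible because the interventions differ substantially, but the primary outcome is an objective clinical measure with low risk of bias".

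Allocation is 1:1 through the electronic data capture system "in blocks of 2, 4 and 6". The list is managed by the department secretary.

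**The concern.** The stated reason why blinding is not feasible is that the interventions differ. That reason applies to participants and to those who treat them. It does not apply to the person holding the probe or to the person running the final model. The article moves from the first group to a general statement of low risk, resting only on the nature of the instrument.

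At follow-up, the person collecting the reading may know the arm, the earlier values and the trial's stated hypothesis that the diet will do better (Introduction). Expectation could then enter when readings are taken or accepted. Such a shift would pass straight into the between-arm difference, and no analysis can remove it afterwards.

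The one safeguard described, the blinded statistician, is tied to a preliminary analysis. As worded, the reported result need not come from the blinded run.

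**Working it through.** **1. What the text supports about who knows what.**

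| Step | Who, on the text | Arm known? |
|---|---|---|
| Screening scan (baseline LSM) | Investigator | No: it decides eligibility and precedes consent and randomisation (Data collection; Table 1) |
| Scans at 3 and 6 months | Investigator, through data collection | Yes: the same role delivers the interventions |
| First preliminary primary analysis | Independent statistician | No |
| Reported primary analysis | Not stated to be the blinded run | Open on the wording |

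The gap lies in the second and fourth rows.

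**2. The plan's own sample size, used here only to fix the scale.** Inputs from Sample size and recruitment: difference 0.8 kPa, SD 1.0 kPa, two-sided α 0.05, power 0.80, 29 per group needed, 35 per group planned. A two-sample t-test at 0.8 kPa needs 25.5, so 26 per group. The unrounded inputs give (0.4 + 2.1)/2 − 0.5 = 0.75 kPa, which needs 28.9, so 29. The stated 29 is therefore reproduced with the unrounded difference. That rounding does not affect this point.

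**3. What a differential reading shift would do.** The documents give no size for such a shift *b*, so 0.1 to 0.3 kPa is an assumption. With no true difference and *n* per arm:

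- SE = SD × √(2/*n*), which is √(2/29) = 0.2626 and √(2/35) = 0.2390.
- Rejection rate = 1 − Φ(1.96 − *b*/SE) + Φ(−1.96 − *b*/SE).
- Example, *b* = 0.2 and *n* = 29: *b*/SE = 0.762, so 0.1154 + 0.0032 = 0.1186.

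| Assumed *b* | 29 per arm, normal (t-test) | 35 per arm, normal (t-test) |
|---|---|---|
| 0.1 kPa | 6.7% (6.6%) | 7.0% (7.0%) |
| 0.2 kPa | 11.9% (11.6%) | 13.3% (13.1%) |
| 0.3 kPa | 20.8% (20.2%) | 24.1% (23.6%) |

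For scale, 0.2 kPa is one quarter of the planned 0.8 kPa (0.2/0.8 = 0.25).

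**4. Block sizes, as a side check.** Lists of 70 allocations were simulated with equally likely block sizes (an assumption) and a recruiter who guesses the under-represented arm. The guess is right 70.1% of the time with blocks 2/4/6, 69.1% with 4/6 and 67.8% with 4/6/8. The share of allocations predictable with at least 75% certainty does fall, from 59% with 2/4/6 to 35% with 4/6/8. That contrast depends on the threshold: it is 59.2% against 59.8% at 70% certainty, and 6.4% against 5.3% at 90%. Dropping the block of 2 changes little.

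**The case against.** **The operator is not named.** That the investigator takes the scan is read from the words on data collection. A dietitian and a physician also take part, Data management speaks of an investigator team, and the full protocol may assign the scan to someone else. This stands as a caution: if an independent operator already scans, saying so would answer most of the point. It does not rescue the article's own claim, which is argued from the instrument alone.

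**The model is fixed in advance.** Statistical methods specifies the primary model, time point and contrast, which limits what an unblinded analyst could change. That is fair, and it makes the analyst limb the lesser one. The word preliminary still leaves open which run is reported.

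**The error rates rest on an assumed shift.** True. They show sensitivity, and are no evidence that a shift occurs.

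**Stronger readings that the documents do not support.**

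- A reader might infer that the baseline LSM could be coloured by knowledge of the allocation, because the article says only when the participant is told. The baseline scan is the screening scan and comes before randomisation, so this fails for the primary outcome.
- A reader might infer that small blocks and a recruiting investigator tilt enrolment towards the diet. Prediction is possible in principle, but nothing shows that it happens or in which direction. Block sizes vary, the system randomises, the secretary manages the list, eligibility depends on a measured LSM window, and the model adjusts for baseline.

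**Conclusion.** The point holds in limited form. On the article's text, the role that delivers the interventions also collects the 3- and 6-month primary outcome with no blinded assessor described, and analyst blinding is promised only for a preliminary run. The low-risk claim therefore lacks support. This does not show that the readings will be biased.

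The size is unknown. Under assumed shifts of 0.1, 0.2 or 0.3 kPa, with SD 1.0 kPa and 29 to 35 per arm, the two-sided type I error would be about 7%, 12–13% or 20–24% instead of 5%. Unblinded readings matter more than the analyst wording, because a blinded statistician cannot correct them. Block size is minor.

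**What to change.** 1. **Analysis.** State that the prespecified primary model in Statistical methods, run by the independent statistician on locked data with arms masked, is the reported primary analysis. Cost: wording, and a coded arm variable in the data transfer.
2. **Follow-up scans.** Take the scan first in the 3- and 6-month visits, with earlier readings hidden. Where a trained operator who does not deliver the intervention is already available, have that person take it. Cost: visit order. The documents do not show that such an operator exists, so this part is conditional and should not be read as a call for new staff. Without one, hiding earlier readings reduces the influence of the earlier values but does not conceal the arm.
3. **Claim.** Replace the low-risk wording with a statement that outcome assessment is unblinded or, if a separate operator is used, say who scans and what that person knows. Cost: one sentence.
4. **Optional and minor.** For future allocations, drop block size 2 and do not give block sizes to recruiters. The best-guess rate falls only from 70% to 68–69%. With 4/6/8, the largest possible final imbalance rises from 3 to 4 participants (half the largest block); with 4/6 it stays at 3.

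The article gives a start in April 2025 and expected completion in July 2027. Changes 1 and 3 need no change to data already collected, and change 2 can protect the scans still to come.

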### Data management

Data will be entered into a data management system (Castor EDC, Amsterdam, The Netherlands) with a consecutive participant code number (no name and any other identifying detail). The participant identification code list, which links the code number to the participant, will be safeguarded by the secretary of the department of Internal Medicine in a ‘master file’. The key to the code is only accessible by the investigators. Study data can only be accessed by the investigator team and staff of the Health Care Inspection, as stated in the informed consent form. Data will be collected and processed in accordance with the General Data Protection Regulation (EU) 2016/679 and the Dutch Act on Implementation of the General Data Protection Regulation. All data will be kept for a maximum of 25 years after the trial has finished.

### Statistical methods

All analyses will be conducted according to the intention-to-treat and per protocol principle. To be included in the per protocol analysis, a participant is required to have at least data available for two time points (baseline and T1 or T2) and to achieve 80% or higher adherence. Participants of the eTRE-MD group are considered adherent to the dietary protocol if they restrict their daily food intake to a window of less than 10 hours—specifically between 7:30 AM and 6:30 PM—on at least 5 days per week. Additionally, they must maintain a daily caloric intake that is at least 400 calories below their estimated energy requirement. Participants of the N/B group are considered adherent to the medication protocol if they consistently take a minimum of two tablets per day, with the exact dosage adjusted according to individual tolerance levels. These adherence data will be used to classify participants for the per protocol analysis and to explore the impact of medication compliance on treatment outcomes. All other non-compliant participants will be excluded from the per protocol analysis. Normality of the data and homogeneity of variances will be tested using Shapiro-Wilks test and Levene’s test. For numerical data, we will use the mean (in case of normal distribution) and median values (in case of non-normal distribution), with respectively the SD and IQR as measures of dispersion.

The primary outcome will be defined as the absolute change in liver fibrosis during 6 months. The difference in liver fibrosis change between the eTRE-MD group and N/B group will be analysed with a linear mixed model adjusted for baseline, with independent variables treatment arm, time point (T1 and T2), and the interaction between treatment arm and time point. The estimated difference between treatment arms in the liver fibrosis change at T2 (6 months) will be calculated using the estimated marginal means. Mixed modelling can efficiently handle data with missing and unbalanced time-points. It corrects for bias when absence of data is dependent on characteristics that are present in the models (missing at random, MAR). The secondary outcomes will be analysed with a linear mixed model adjusted for baseline, with independent variables treatment arm, time point (T1 and T2), and the interaction between treatment arm and time point. The estimated difference between treatment arms will be calculated using the estimated marginal means.

To account for heterogeneity in metabolic profiles, cardiometabolic condition (type 2 diabetes, hypertension, dyslipidaemia or obesity) will be included as a covariate in all primary and secondary outcome analyses. Outcomes will be analysed using linear mixed models with treatment arm, time point (T1 and T2), and their interaction as fixed effects, adjusted for baseline values. An interaction term between treatment arm and cardiometabolic condition will be explored to assess potential differential treatment effects across subgroups. Given the limited sample size, stratified analyses will not be performed unless sufficient power is available. Participants with multiple conditions will be included in the overall model and appropriately coded for subgroup membership. Sensitivity analyses may be conducted to evaluate the robustness of findings in overlapping vs non-overlapping subgroups.

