**Methods and analysis:**

We will conduct a randomised controlled trial with a planned sample size of 70 overweight (Body mass index, BMI >27 kg/m2) adults aged 18–75 years with T2D, hypertension, dyslipidaemia or obesity and moderate to severe liver fibrosis, measured as LSM (>7.0 kPa and <13.6 kPa). The diet group will receive eTRE-MD, with a 10-hour eating time restriction (8AM–6PM). The medication group will receive 32 mg/360 mg of N/B (after a dose increase period following Summary of Product Characteristics). The main study endpoint is the between-group difference in liver fibrosis (kPa) from baseline to 6 months. Secondary endpoints are liver steatosis, weight, body composition, cardiovascular risk factors, quality of life, patient satisfaction and compliance. General linear models for repeated measurements will be applied for statistical analysis of the data.

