Lifestyle modification–including weight loss, dietary changes, physical exercise and discouraging alcohol consumption–is currently the primary recommended treatment for MASLD according to the latest guidelines from the European Association for the Study of the Liver (EASL).^7^ Most guidelines highlight the Mediterranean diet as an effective dietary intervention for MASLD. A recent meta-analysis supports this recommendation, showing that the diet significantly reduces liver fat and insulin resistance in individuals with MASLD, independent of weight loss or amount of visceral fat.^8^ Furthermore, long-term adherence to the Mediterranean diet combined with carbohydrate restriction appears more effective in reducing liver fat than a fat restricted diet alone.^9^ In addition to the Mediterranean diet, other nutritional strategies have shown promise. Caloric restriction through intermittent fasting may benefit individuals with MASLD.^10^ Observational studies suggest that shifting food intake to earlier in the day is associated with a lower risk of fatty liver disease, and that intermittent fasting improves hepatic outcomes in people with T2D.^10 11^ Intermittent fasting is an umbrella term that encompasses a range of dietary interventions aimed at extending the fasting period. Among these interventions, eTRE—which limits the daily eating window to less than 10 hours, ending in the late afternoon—seems to be the most promising strategy. In a 2-week proof-of-principle controlled eating study, eTRE led to significant improvements in metabolic health, including glycaemic markers, among overweight prediabetic men, independent of changes in body weight.^12^ Additional evidence suggests that eTRE enhances insulin sensitivity and glycaemic control in individuals with T2D and promotes weight reduction in people with obesity.^13^,^16^ Given that weight loss remains a cornerstone in the management of MASLD, these findings are clinically relevant. Histological data indicate that a 3%–5% reduction in body weight can improve liver steatosis, while losses exceeding 10% may lead to regression of steatohepatitis and fibrosis.^17^ Despite these promising outcomes, only a limited number of randomised controlled trials have evaluated the effects of eTRE in individuals with MASLD. Current evidence supports its efficacy in reducing intrahepatic fat; however, its impact on liver fibrosis has not yet been clarified.^18 19^ A recent 12-week intervention combining eTRE with a hypocaloric Mediterranean diet demonstrated a significant reduction in liver fibrosis, though the short duration limits conclusions regarding long-term effects.^20^ Therefore, further long-term research is needed, combining eTRE with a Mediterranean diet to investigate the most potential dietary strategy for people with MASLD.

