#### Diet group

Participants in the diet group will follow with a calorie restricted Mediterranean diet, with an eating window between 8 am and 6 pm for a period of 6 months. Participants are asked to stop eating at 6 pm. This results in a daily fasting window of approximately 14 hours. During the fasting time, only calorie-free drinks will be allowed. A daily calorie restriction of 500 kcal will be applied, based on the estimated energy requirement calculated using the WHO equation for participants with a BMI ≤30 and the Harris-Benedict equation for those with a BMI >30.^26^ The diet will be based on the Mediterranean food pyramid,^27^ emphasising high-fibre foods such as fresh fruits and vegetables, unprocessed whole grains, beans, seeds, herbs and spices, while limiting processed foods, red meat, sweets and alcohol. At baseline, participants receive a detailed explanation of the dietary protocol, two sample daily meal plans, recipes and a food-exchange list. Dietary adherence is assessed at the 3-month and 6-month follow-up visits using food diaries in which participants record all foods consumed and the corresponding times. The eating window is additionally evaluated at each visit through a questionnaire assessing the average latest eating time and the number of days per week participants adhere to the fasting regimen. Participants receive guidance from a registered dietitian to support correct implementation of the intervention. Consultations take place during the in-person study visits at baseline, 3 months and 6 months. Throughout the intervention period, participants may also contact the study dietitian by telephone for ongoing support. During the entire programme, 60 min of exercise per day is advised. Physical activity will be measured for 1 week with the Activ8 Activity Tracker GEN2 at baseline and at the end of the study.

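### The diet arm's per-protocol eating-window rule gives two limits that do not match (under 10 hours, and clock times 11 hours apart), so adherence is undetermined for eating periods of 10 to 11 hours

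*Protocol article*

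**What the plan says.** The Diet group section prescribes a calorie-restricted Mediterranean diet "with an eating window between 8 am and 6 pm for a period of 6 months", asks participants to stop eating at 6 pm, and adds: "This results in a daily fasting window of approximately 14 hours". The Abstract gives the same clock times and calls them a 10-hour restriction. These two places agree.

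Statistical methods plans every analysis both by intention to treat and per protocol. Entry to the per-protocol set requires data at baseline and at least one later visit, and the participant has "to achieve 80% or higher adherence". For the diet arm, adherence means eating within "a window of less than 10 hours—specifically between 7:30 AM and 6:30 PM", "on at least 5 days per week", together with a daily intake at least 400 kcal below the estimated requirement. Participants who do not comply are left out of the per-protocol analysis.

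The Introduction describes early time-restricted eating in general as an approach that "limits the daily eating window to less than 10 hours, ending in the late afternoon".

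**The concern.** The adherence sentence states a length and then, with the word for a more exact restatement, gives clock times that span a longer period. Neither figure equals the prescribed 10 hours: one is strictly below it and the other is an hour above it. The article does not say which figure governs, whether both must hold, or whether the clock times are a tolerance around the prescribed window.

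The per-protocol comparison of liver stiffness is at stake. The ambiguity touches the diet arm only, so the choice of reading changes the composition of one side of the comparison. Participants and the treating investigator know the allocation, and the article promises blinding only for a first preliminary analysis of the primary outcome. An adherence rule in such a trial should leave no choice open when participants are classified.

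**Working it through.** No sample-size or power formula is involved. The check is clock arithmetic, followed by classification of example days under each reading.

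**Inputs**
- Prescribed window: 08:00 to 18:00 (Abstract; Diet group).
- Length limit: strictly under 10 h (Statistical methods).
- Clock limits: 07:30 to 18:30, taken as inclusive (Statistical methods).

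**The plan's own figure.** 18:00 − 08:00 = 10.0 h of eating, and 24 − 10 = 14.0 h of fasting. This reproduces the 10-hour restriction and the fast of about 14 hours, so the prescription is internally consistent.

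**The adherence rule.** 18:30 − 07:30 = 11.0 h of eating, and 24 − 11 = 13.0 h of fasting. The clock limits are 11.0 − 10.0 = 1.0 h longer than the prescribed window, which is 30 minutes at each end.

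**Classification of example days**

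| Eating period | Length | Length limit only | Clock limits only | Both required |
|---|---|---|---|---|
| 08:00–17:45 | 9.75 h | adherent | adherent | adherent |
| 08:30–18:20 | 9.83 h | adherent | adherent | adherent |
| 08:00–18:00 (full prescribed window) | 10.0 h | not adherent | adherent | not adherent |
| 08:00–18:30 | 10.5 h | not adherent | adherent | not adherent |
| 07:30–18:30 | 11.0 h | not adherent | adherent | not adherent |

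Three things follow.
1. A day spent eating across the whole prescribed window fails on two of the three readings, because 10 is not less than 10.
2. On those same two readings, 08:30–18:20 passes although it runs 20 minutes past the prescribed stop, while 08:00–18:00 fails although it never leaves the prescribed window.
3. Status depends on the reading for every eating period from 10 h up to and including 11 h that lies inside 07:30–18:30. Periods under 10 h inside those times are adherent on all three readings.

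**The case against.** The strongest defence is that the clock times are a deliberate tolerance: the prescribed window plus 30 minutes at each end. The calorie rule in the same passage is relaxed in a similar way, since a 500 kcal restriction is prescribed and 400 kcal is enough for adherence. This is a plausible reading, and on it the rule is lenient rather than mistaken. A reader might infer that the per-protocol set is wrong whichever reading is taken. The documents do not support that. What stands is that the tolerance is not stated, and that this reading requires the length limit in the same sentence to be set aside.

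It can also be said that the limits are not mutually exclusive, since an eating period under 10 hours inside 07:30–18:30 meets both. That is correct, but the combined reading still classes the full prescribed window as non-adherent.

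A reader might further infer that the length limit would remove compliant participants in general. It would not. The prescription sets a window within which to eat, so anyone who starts later or finishes earlier has an eating period under 10 hours and passes. Only days that use the full 10 hours are affected among those inside the prescribed window, and the rule asks for 5 days per week rather than 7.

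The Introduction's under-10-hour description might look like another contradiction. It is background on a class of interventions, not a rule of this trial, and carries no weight here.

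Finally, a statistical analysis plan that is not shown may settle the derivation. It therefore cannot be said that the choice will be made after the data are seen. But the point does not rest on missing detail: the article states a numerical rule, and its figures do not agree.

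**Conclusion.** The point stands in a limited form. The two limits in the adherence sentence do not match each other, and wherever the length limit applies, a participant who uses the whole prescribed window is classed as non-adherent. Diet-arm per-protocol status is therefore indeterminate for eating periods of 10 to 11 hours inside the clock limits.

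The number of participants affected cannot be computed. The article gives no distribution of eating times, so applying any assumed share to the 35 planned diet participants would be a guess. The window is also not the only condition: the calorie criterion, the 80% adherence threshold and the requirement for data at two time points apply too, and a participant who fails one of these does not change status with the reading of the window.

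The effect is confined to the diet arm's per-protocol set. The intention-to-treat analysis, planned for every outcome, is unaffected, as are the endpoint, the randomisation and the model. The sentence should be corrected, but it does not threaten the trial's conclusions by intention to treat. The verdict assumes that the article reproduces the operative adherence rule and that the clock limits are inclusive.

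**What to change.** Before any analysis by arm, reconcile the adherence sentence in Statistical methods with the window in the Abstract and the Diet group section. The revised sentence should state:
- which limit governs, or that both must hold;
- whether the 7:30 AM and 6:30 PM times are a tolerance around the prescribed window;
- a length limit, if one is kept, that is consistent with those clock times, so that a participant who follows the prescribed window counts as adherent.

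A rule with both a length limit and clock limits is acceptable provided the figures fit together. Which window the trial should prescribe is for the sponsor. The requirement here is only that the prescription and the adherence rule agree.

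The cost is one sentence in the protocol or analysis plan and a matching derivation rule. The food diaries already record eating times, so no new data are needed.
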